### Treatment

Immunosuppressive treatment (see Figure 1) will be initiated at reperfusion of the graft starting with 500 mg methylprednisolone and 20 mg basiliximab given intravenously. The latter will be repeated on the 4th post-operative day (POD).

**Figure 1 F1:**
[figure not shown]
**Scheme of proposed reno-protective immunosuppressive regimen without CNI**. Abbr.: EC-MPS, enteric-coated mycophenolate sodium; POD, post-operative day; BW, body weight; q12h and q24h, every 12 or 24 hours.

Maintenance immunosuppression includes EC-MPS, everolimus, and prednisolone. Since systemic exposure of MPAmay be reduced in patients receiving immunosuppressive regimens with reduced dose CNI or without CNI [22] EC-MPS will be given at an increased dose, i. e., 1080 mg q12, starting within 24 hours after OLT.

Earliest, on day 10 after OLT everolimus will be introduced with a loading dose of 5 mg/d. Thereafter a dosage of 2 mg/d in two doses will be administered, aiming at 24 hours trough levels for everolimus between 4 and 8 ng/mL. Steroids (non investigational medicinal product) will be started on day 1 after transplantation with 1 mg/kg body weight and will be tapered every 2 days for 5 mg to a dosage of 20 mg and for 2.5 mg every two days to 7.5 mg. Thereafter the dosage will be reduced to 5 mg and 2.5 mg for 1 week each and eliminated thereafter.

Additionally, every patient will receive Cytomegalo virus (CMV) prophylaxis and prophylaxis against Pneumocystis carinii infection during the first 3 months after liver transplantation.

### Objectives and endpoints

The primary objective of this pilot study is to evaluate the safety and to investigate the preliminary efficacy of a CNI-free immunosuppressive *de-novo *regimen in patients with impaired renal function undergoing liver transplantation. The primary endpoint was thus defined as the incidence of biopsy proven steroid resistant acute rejection(s) within the first 30 days.

Secondary objectives of the trial are the assessment of adverse reactions and renal function under the proposed study regimen. Secondary endpoints will be evaluated after in one interim analysis and after the end of the follow-up period, i. e., one year, and include mortality, the incidence of infection, treatment failure (defined as re-introduction of CNI), wound-healing disturbances, hepatic artery stenoses, and hemato-lymphatic side effects. Furthermore kidney damage will be assessed by the incidence and length of renal replacement therapy and the estimation of renal function using the Modification of Diet in Renal Disease (MDRD) formula. Finally liver allograft function will assessed by measurement of liver enzymes, bile excretion, and coagulation assays.

All end-points will be compared to reference values of CNI based immunosuppression obtained from a meta-analysis [25].

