### Safety and efficacy of the investigational medicinal products

Basiliximab, everolimus, and enteric-coated mycophenolate sodium (EC-MPS) are the investigational medicinal products that will be evaluated in this clinical trial.

Basiliximab has been shown to reduce the incidence of acute rejection with no clinically relevant safety or tolerability concerns [18,19]. Both IL2R antibodies, i. e., basiliximab and daclizumab, have also been shown to prevent acute rejection even when CNIs are delayed for five or more days after OLT [14,17]. Since daclizumab has been withdrawn from the market we use basiliximab as standard immunoprophylaxis in our transplant center and in this study.

For maintenance immunosuppression the proposed regimen will include the mTOR inhibitor everolimus. Phase I and II trials of therapy with everolimus in *de novo *liver transplant recipients implicate efficacy and good tolerability of this immunosuppressant [20,21]. We decided to use everolimus and not sirolimus because i) dose adjustments are more convenient with the shorter biological half-life of everolimus (28 hrs) compared to sirolimus (61-72 hrs); ii) increased rates of hepatic artery thrombosis and wound healing disturbances have been observed in a trial involving sirolimus but not in trials involving everolimus [20,21].

Nonetheless everolimus therapy will be delayed until the 10th postoperative day for safety reasons. Concomitantly the antimetabolite EC-MPS will be used instead of the commonly used mycophenolate mofetil (MMF). MMF may cause considerable gastro-intestinal adverse reactions, e. g. diarrhea, and reduction or discontinuation is not uncommon even in the immediate posttransplant period. EC-MPS has been shown to cause less adverse reactions und thus compliance with the study protocol may be better.

EC-MPS will also be administered in a higher than usual dose, i. e., 2160 mg/day instead of 1440 mg/day in two doses, because van Gelder et al. suggested that higher MPAexp osures in the early post-transplantation period would be required in patients on reduced rather than standard cyclosporine doses [22].

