## Methods & Design

Research was carried out in compliance with the Helsinki Declaration. After completion of trial design and approval by the competent authorities in Germany and the European Union an ethics vote was obtained from the ethics committee at the University Medical Center, Göttingen, Germany before start of enrollment. Only patients who meet the inclusion and exclusion criteria (see Table 1) are considered for enrollment. After enrollment patients will be followed-up for one year. The schedule for all study related activities and data collection is listed in Table 2.

**Table 1 T1:** Criteria for inclusion and exclusion of patients.

Inclusion criteria	Exclusion criteria
1. Patients undergoing primary liver transplantation.	1. Pregnant or nursing women.
2. Patients older than 18 years.	2. Patients with a psychological, familial, sociologic or geographic condition potentially hampering compliance with the study protocol and follow-up schedule.
3. Patients with a hepatorenal syndrome.	3. Patients under guardianship, i. e., individuals who are not able to freely give their informed consent.
4. Female patients of childbearing potential willing to perform a highly effective contraception during the study and 12 weeks after conclusion of study participation. ^†^	4. Patients with pre-transplant renal replacement therapy > 14 days.
5. eGFR < 50 ml/min at the time point of transplantation.	5. Patients with a reason for renal impairment other than a hepatorenal syndrome.
6. Serum creatinine levels > 1.5 mg/dL at the time-point of transplantation.	6. Patients with a known hypersensitivity to any of the investigational medicinal products.
	7. Patients with thrombocytopenia (<50.000/nl), hypertriglyceridemia (> 350 mg/dl), or hypercholesterinemia (> 300 mg/dl), and patients with signs of hepatic artery stenosis prior to initiation of therapy with everolimus.

^† ^A highly effective method of birth control is defined as those which result in a low failure rate (i.e. less than 1 per year) when used consistently and correctly such as implants, injectables, combined oral contraceptives, hormonal intrauterine devices (IUDs), sexual abstinence or vasectomised partners in accordance to CPMP/ICH/286/95.

**Table 2 T2:** Schedule of study related activities and data collection.

Study activity	Day										Month		
		
	-3-0	1	2	3	5	10	14/15	20/21	25/26	30	3	6	12
Patient baseline characteristics and transplant data													

Informed consent	*												

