### Adverse events

All adverse events (AE) are recorded. Events related to the initial diagnosis for liver transplantation, to the transplantation procedure itself, or problems associated with routine procedures after transplantation, i.e. liver biopsy, are not to be noted as AE or serious adverse event (SAE) unless the investigator deems the events to be a cause of the study drug. All SAE potentially associated with the application of study medication must be documented and the sponsor has to be informed by the principal investigator within 24 hours. The sponsor will notify all concerned investigators, the Ethics Committee, and competent authority of findings that could adversely affect the health of subjects. AE will be analysed in an interim analysis and at termination of the trial.

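### Hepatic artery thrombosis is cited in the choice of everolimus but not named as an endpoint, and the adverse-event rule makes its recording depend on attribution

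*Protocol article*

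**What the plan says.** Four places in the protocol article bear on this point.

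- **Safety and efficacy of the investigational medicinal products.** One of the two reasons for preferring everolimus to sirolimus is that "increased rates of hepatic artery thrombosis and wound healing disturbances have been observed in a trial involving sirolimus but not in trials involving everolimus". The text goes on: "Nonetheless everolimus therapy will be delayed until the 10th postoperative day for safety reasons".
- **Objectives and endpoints.** The secondary endpoints include "wound-healing disturbances, hepatic artery stenoses, and hemato-lymphatic side effects". Thrombosis is not in the list.
- **Methods & Design, Table 1.** The last exclusion criterion covers "patients with signs of hepatic artery stenosis prior to initiation of therapy with everolimus". Here too the arterial condition is stenosis.
- **Adverse events.** The section opens with "All adverse events (AE) are recorded" and then makes an exception. "Events related to the initial diagnosis for liver transplantation, to the transplantation procedure itself, or problems associated with routine procedures after transplantation" are not to be noted as AE or SAE "unless the investigator deems the events to be a cause of the study drug". I read that last phrase in its evident sense, that the investigator attributes the event to the drug. AEs feed an interim analysis and the final analysis. Under Quality assurance, an independent board monitors the SAE reports.

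**The concern.** The rationale pairs two harms, and only one of them reaches the endpoint list under its own name. The arterial harm reappears as a different event: on a literal reading, an artery occluded by thrombus is not a stenosis. The hepatic artery is reconstructed during the transplant, so a thrombosis is readily classed as related to the procedure. The AE exception then applies, and only the investigator's causality judgement brings the event back in. The trial is open-label, single-centre and single-arm, so there is no control group against which to check that judgement.

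Safety is part of the primary objective, and the study rationale says the trial is meant primarily to show safety before a phase III trial. A harm cited in the choice of drug should be counted in a way that does not depend on attribution.

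**Working it through.** **Step 1. Follow one thrombosis through the stated rules.**

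| How the event is judged and ends | Named endpoint? | AE/SAE, and so interim analysis and safety board? | Visible elsewhere? |
|---|---|---|---|
| Attributed to study drug | Not as worded | Yes: AE, and SAE if serious | Yes |
| Judged procedural; graft loss or death follows | Not as worded | No | In graft survival or mortality, but not as thrombosis |
| Judged procedural; graft and patient survive | Not as worded | No | Possibly on ultrasound or in liver tests, but no stated count uses these |

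Table 2 makes ultrasound mandatory on days 1, 2, 3 and 10, with further examinations on pathological findings or indication. The Treatment section starts everolimus on day 10 at the earliest. Mandatory imaging therefore falls almost wholly before exposure to everolimus. Later detection rests on clinical indication.

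**Step 2. The plan's own figure.** The only design number used here is the maximum of 29 patients (9 + 20). With p0 = 0.80, p1 = 0.95, α = 0.05 and β = 0.2, an exact search for the optimal two-stage design returns the stated one: continue if more than 7 of 9 succeed, and conclude success if more than 26 of 29 do. Its exact type I error is 0.0486 and its power 0.802. Nothing in that design depends on this point.

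**Step 3. How many events are at stake.** The documents give no thrombosis rate q. I assume 3% to 10% for illustration, at any time after transplantation.

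- Expected events in 29: 29 × 0.03 = 0.87; 29 × 0.10 = 2.9.
- Chance that at least one occurs, 1 − (1 − q)^29: 59% at 3%, 77% at 5%, 95% at 10%.
- If the trial stops after stage I: 9 × 0.03 = 0.27 to 9 × 0.10 = 0.9 events, with a 24% to 61% chance of at least one.

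These are chances of occurrence, not of loss. They include events before day 10, which cannot be due to everolimus.

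**Step 4. What incomplete recording would do.** The documents give no basis for a loss rate. Assume that a fraction c of events is recorded, so that the chance of recording at least one is 1 − (1 − cq)^29. With c = 0.5:

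- q = 5%: 1 − 0.975^29 = 52%, against 77% with full recording.
- q = 10%: 1 − 0.95^29 = 77%, against 95% with full recording.

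**The case against.** The strongest case on the other side has four parts.

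1. **The harm is not reported for the trial drug.** A reader might infer that the article names thrombosis as the risk of mTOR inhibitors as a class. It does not. It reports the finding from a sirolimus trial, beside wound-healing disturbances, and says that everolimus trials did not show it. The day-10 delay is put down only to safety reasons; the link to thrombosis comes from the word that opens the sentence. This stands and limits the claim. It does not explain why one of two paired harms became an endpoint under its own name and the other did not.

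2. **The event would not vanish.** A reader might infer that thrombosis would be recorded nowhere. That is only the worst case: the event must be judged procedural and lead to neither graft loss nor death. Drug-attributed events are AEs, graft survival and mortality are assessed, and ultrasound and liver tests are scheduled. This also stands. However, apart from the drug-attributed AE, none of these routes yields a count of thromboses.

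3. **The article condenses a fuller protocol, and the endpoint list is open.** It is introduced as a list of inclusions, and the full protocol may define the arterial endpoint more widely. That is a fair caution about the endpoint wording. It does not repair the AE exception, which is stated outright.

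4. **The item is exploratory.** Only the primary endpoint is confirmatory. This is correct, and it sets the weight of the point.

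**Conclusion.** The point holds as a gap between three stated passages. As written, the counting of hepatic artery thrombosis depends on one unblinded attribution in an uncontrolled trial whose primary objective includes safety. A thrombosis judged procedural can miss the endpoint, the AE analyses and the safety board's SAE review, and then appears at most unlabelled, through graft loss or death.

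The size is modest and rests on an assumed rate. At 3% to 10%, about 1 to 3 events of any timing would be expected if all 29 patients are enrolled, and fewer after a stage I stop. With so few events, losing one or two could remove the signal. How many would be lost cannot be derived from the documents.

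A reader might go further and infer that the trial would report a false zero of 29 with a reassuring upper limit. The documents do not support this: since thrombosis is not a listed endpoint, they call for no such figure. For reference, the exact one-sided 95% upper limit for 0/29 is 1 − 0.05^(1/29) = 9.8%. The Agresti–Coull method named in the Statistical analysis plan section gives a two-sided 95% upper limit of about 13.9%.

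Sample size, error rates, stopping rule and primary conclusion are unaffected. This is an inexpensive improvement to safety recording, not a flaw in the primary analysis.

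**What to change.** Reconcile the drug rationale, the endpoint list and the AE rule as follows.

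- Word the secondary endpoint as hepatic artery thrombosis or stenosis.
- Record every such event in every patient, with its date, whether it fell before or after the start of everolimus, and its attributed cause.
- Exempt these events from the procedure-related exclusion in the Adverse events section, so that they reach the interim analysis and, when serious, the safety board.

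The cost is a change of wording and one case report form item. No extra examination is needed and the sample size stays at 29. The drawback is that some events due to surgery will be counted. Recording date and attribution lets the report show them separately.

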### Statistical analysis plan

The confirmatory analysis will be performed for the per-protocol population. All statistical analyses will be performed with a type I error *α *= 0.05 and, where appropriate, a non-inferiority margin of *δ *= -0.1 will be assumed.

All rates will be tested in an approximate one sample design test for non-inferiority [27] against reference values obtained from a pooled meta-analysis of trials with immunosuppressive regimen based on CNI [25].

Confidence intervals will be calculated by the method of Agresti and Coull [28]. The only confirmatory analysis will concern the primary endpoint; all other analyses will be exploratory.

Continuous secondary end-points will be compared to reference values with student's T test unless there is considerable evidence for a non-parametric distribution. Event-time data, i. e., time to acute rejection, patient, and graft survival will be estimated by the Kaplan-Meier method.

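### Renal and mortality endpoints in patients selected for hepatorenal syndrome are tested against CNI reference values that the article describes without any renal restriction

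*Protocol article*

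**What the plan says.** Four parts of the protocol article bear on this point.

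- **Comparator.** Objectives and endpoints: "All end-points will be compared to reference values of CNI based immunosuppression obtained from a meta-analysis". The renal endpoints listed there are the incidence and length of renal replacement therapy and the "estimation of renal function using the Modification of Diet in Renal Disease (MDRD) formula". Mortality is also a secondary endpoint.
- **Tests.** Statistical analysis plan: "All rates will be tested in an approximate one sample design test for non-inferiority", against "reference values obtained from a pooled meta-analysis of trials with immunosuppressive regimen based on CNI". For the rest, "Continuous secondary end-points will be compared to reference values with student's T test", with an exception where the data are clearly unsuited to a parametric test. The margin is -0.1 where one applies and alpha is 0.05. Only the primary endpoint is confirmatory; everything else is declared exploratory.
- **Population.** Table 1 in Methods & Design lists as inclusion criteria "Patients with a hepatorenal syndrome", "eGFR < 50 ml/min at the time point of transplantation" and serum creatinine above 1.5 mg/dL. It excludes renal impairment from any other cause.
- **Reference population.** The Sample size calculation and Statistical analysis plan sections describe the meta-analysis only by its CNI-based regimens. No renal restriction, matching or adjustment is mentioned.

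**The concern.** A one-sample test asks whether these patients differ from a fixed number. The answer bears on the regimen only if that number is what the same kind of patient would show on CNI. Here the patients are chosen for poor renal function, and nothing in the article indicates that the reference patients were. Renal function after transplantation, need for renal replacement therapy and survival would all be expected to depend on renal function beforehand. The article's own Background points this way: it links renal dysfunction to premature death and expects the benefit of sparing CNI to be larger when pretransplant kidney function is compromised.

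With no concurrent control, nothing in the analysis separates case mix from treatment. Sparing the kidney is the reason for the regimen, and the article intends these data to help plan a phase III trial. A case-mix difference read as an effect of the regimen, or one that hides such an effect, would mislead that planning.

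**Working it through.** **1. The plan's own figure.** The design has 9 + 20 patients, continues if more than 7 of 9 succeed, and is positive if more than 26 of 29 succeed, with p0 = 0.80 and p1 = 0.95. The probability of a positive trial is the sum over x = 8, 9 of P(X1 = x) × P(X2 ≥ 27 − x), where X1 ~ Bin(9, p) and X2 ~ Bin(20, p).

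- At p = 0.80: 0.0486 (type I error, stated 0.05).
- At p = 0.95: 0.802 (power; stated beta 0.2).

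The design reproduces. It uses fixed rates for steroid-resistant rejection, so the present point does not change it.

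**2. Inputs for the secondary tests.** From the article: n = 29, alpha = 0.05, margin 0.1. Not in the article, and therefore assumed:

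- the gap d, in SD units, between the reference mean used and the mean that comparable patients would have on CNI;
- the event-free rate of comparable patients on CNI (80%);
- a two-sided t test and a one-sided non-inferiority test, since sidedness is not stated;
- all 29 patients contributing.

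**3. Continuous endpoints such as eGFR.** Suppose the regimen has exactly the same effect as CNI in these patients. The t statistic then follows a noncentral t distribution with 28 degrees of freedom and noncentrality d × √29. The two-sided critical value is 2.048. At d = 0.5 the noncentrality is 0.5 × 5.385 = 2.69.

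| Reference off by (SD) | Noncentrality | Chance of a significant but spurious difference |
|---|---|---|
| 0 | 0 | 5% |
| 0.25 | 1.35 | 26% |
| 0.5 | 2.69 | 74% |
| 0.75 | 4.04 | 97% |
| 1.0 | 5.39 | >99% |

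For scale, if the SD of eGFR were 20 mL/min (assumed), 0.5 SD is 10 mL/min. An observed gap of that size gives t = 10 / (20/√29) = 2.69, p = 0.012.

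**4. Rates.** On the event-free scale, the boundary is b = reference − 0.1. Non-inferiority is declared if the observed rate exceeds b + 1.645 × √(b(1 − b)/29). The true rate is set to 80%, equal to that of comparable patients on CNI.

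| Reference used | b | Needed out of 29 | Chance of declaring non-inferiority |
|---|---|---|---|
| 80% (right) | 0.70 | 25 | 28% |
| 85% | 0.75 | 26 | 14% |
| 90% | 0.80 | 27 | 5% |

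Taking the last row: 0.80 + 1.645 × 0.0743 = 0.922, and 0.922 × 29 = 26.7, so 27 are needed. A reference 10 points too favourable cuts the chance for a truly equivalent regimen from 28% to 5%.

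**The case against.** **The analyses are exploratory.** The article says so, and it reserves confirmation for a later randomised trial, so no secondary p-value can formally establish harm or benefit. That stands and limits the weight of the point. But the label deals with error rates across many tests. It does not remove bias from a poorly matched reference.

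**The meta-analysis cannot be inspected here.** This also stands. That its patients were not selected for renal impairment is an inference from how the article describes it, not something the article states.

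**Every size is assumed.** This is correct. The article gives no renal reference value and no SD, so the tables show sensitivity, not an expected error.

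**Part of the remedy is already there.** Agresti-Coull intervals are planned, and the t test may be set aside for unsuitable data. Both help with reporting, but neither changes the comparator.

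**A stronger reading about dialysis.** Table 1 excludes only "Patients with pre-transplant renal replacement therapy > 14 days", so shorter pretransplant dialysis is allowed, and eGFR is scheduled at every visit. A reader might infer that MDRD values obtained on dialysis will be analysed as true renal function. The article does not say so, nor does it say that they are excluded. Such handling is commonly left to the full protocol or analysis plan, which are not shown, so this is not a finding.

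**Conclusion.** The comparison is badly chosen for the renal and mortality endpoints. The text positively fixes it, so it is not a detail left open. With a single arm and a reference described without renal restriction, a difference from that reference cannot be attributed to avoiding CNI, and a lack of difference cannot be taken as equivalence.

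Under the assumptions above, an offset of 0.25 to 0.5 SD raises a nominal 5% t test to a 26% to 74% chance of a spurious difference. A reference rate 5 to 10 points too favourable lowers the chance of declaring non-inferiority from 28% to between 14% and 5%. The direction and size of any real offset are unknown.

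A reader might go further and call the renal results uninterpretable. The article does not support that: the incidence and duration of renal replacement therapy and the course of eGFR from baseline can still be described. What fails is the reading of the external test as an effect of the regimen. The point deserves correction but has modest weight, because these endpoints are secondary and exploratory and the 9 + 20 primary design is untouched.

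**What to change.** Limit the two general statements, in Objectives and endpoints (all endpoints compared) and in the Statistical analysis plan (all rates tested), and apply the same limit to the t-test sentence, so that renal and mortality endpoints are not tested against the meta-analysis. In their place:

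- report the incidence and length of renal replacement therapy, and mortality, as estimates with confidence intervals;
- report eGFR as within-patient change from the day -3 to 0 value, with a confidence interval, using measurements already in Table 2;
- describe that change as descriptive only, because recovery of hepatorenal syndrome after transplantation and regression to the mean from the eGFR entry limit could both produce improvement under any regimen;
- make an outside comparison only where the reference population has comparable pretransplant renal function, and state the basis for that.

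The cost is a change of wording, with no new measurements and no change to the sample size. What is given up is an exploratory p-value against an outside reference.
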